## B. Attention & Memory

### ① Cambridge Neuropsychological Test Automated Battery (CANTAB)

A touchscreen-based cognitive assessment system primarily evaluates cognitive functions such as

memory, judgment, and attention using non-verbal stimuli through a computer interface.

The sequence of CANTAB is as follows :MOT→ DMS → RVP → PRM → RTI →SWM → PAL .

I. Motor Screening (MOT)

: This test involves a flashing "X" on a computer screen that requires participants to touch the "X" with their finger whenever it appears. The test is conducted a total of 13 times, with the initial 3 times serving as practice sessions. The final 10 trials are used for evaluation purposes.

II. Delayed Matching to Sample (DMS)

: This item evaluates visual memory and takes approximately 10 minutes to complete.

A picture appears in the box on the computer screen, and below it, there are 4 options. Remember the color and shape of the picture in the upper box, then choose the same picture from the options below. This task is conducted a total of 23 times, with 3 practice trials and 20 evaluation trials.

III. Rapid Visual Information Processing (RVP)

: This test evaluates attention and takes approximately 7 minutes to complete.

In this test, a square box on the computer screen displays numbers from 1 to 9 repeatedly. When a predetermined sequence of three numbers appears in consecutive order, press the button.

IV. Pattern Recognition Memory (PRM)

: This task assesses visual memory and takes approximately 5 minutes to complete.

A square box appears in the center of the screen, and various images are presented one by one inside that box. Your task is to remember which image you saw and then select the previously displayed image from the options provided.

V. Reaction Time (RTI)

The test takes 5 minutes. While holding down the right button on the press pad with your dominant hand, a yellow circle will flash and appear inside a white circle. When this happens, release the press pad button and quickly press the spot where the yellow circle appeared.

VI. Spatial Working Memory (SWM)

: This test evaluates executive function and takes 8 minutes. When you press the square, it will either

be empty or contain a blue square. If a blue square appears, fill in the black bar below it.

## VII. Paired Associates Learning (PAL)

: This assesses visual memory and takes 10 minutes. When 6 white boxes appear on the screen, two of them will contain different pictures. Remember which picture appeared in which box. Later, a picture will be shown in the center of the screen, and you need to select the box where that picture was originally shown. There are no practice trials, and you will do this a total of 5 times. As the rounds progress, the number of pictures increases. You can go up to a maximum of 6 rounds, but if you fail more than 6 times, the test will end for that round.

### ② SVLT (Seoul Verbal Learning test) and RCFT(Rey Complex Figure test)

The Seoul Verbal Learning Test and Rey Complex Figure Drawing Test will be conducted to assess the suitability for participation in this clinical trial. If the test results from within 3 months of the date of consent acquisition are available, there is no need to repeat the tests.

## C. Frontal/executive test

### ① COWAT (Controlled Oral Word Association Test)

This test evaluates how many words a participant can voluntarily speak within 60 seconds that belong to given semantic categories (animals, supermarket) and phonemic categories (ㄱ, ㅇ, ㄴ) or start with the provided phonemes. This test is a representative assessment of frontal lobe functions.

·animal

·supermarket

·phonemic (ㄱ, ㅇ, ㄴ)

### ② Stroop test

This test assesses how reaction time varies based on attention and inhibitory abilities. For instance, if the word "빨강" (meaning red) is printed in yellow rather than red, participants need to inhibit their automatic reading response and instead name the color. This test evaluates inhibitory control and attention.

③ Trail making test (TMT)

The Trail Making Test (TMT) is an assessment where scattered numbers and days of the week on a sheet of paper need to be connected in order. TMT-A involves connecting randomly arranged numbers from 1 to 15 in the correct order, while TMT-B requires alternating connections between numbers 1 to 8 and days of the week "월" to "일". This test evaluates cognitive flexibility, attention, and visual-motor coordination.

④ Cambridge Neuropsychological Test Automated Battery (CANTAB)

(6) Korean version of Geriatric Depression Scale (K-GDS) short form

The Geriatric Depression Scale (GDS) short form consists of 15 questions. The highest score indicating very severe depression is 15 points, with a cut-off point at 8 points. This assessment is used to evaluate the presence and severity of depression in geriatric populations. [12]

Depression is one of the most common behavioral symptoms seen in Alzheimer's disease. Onset of depression in later life could be a precursor or a significant risk factor for Alzheimer's disease. When depression co-occurs with Alzheimer's disease, patients may experience more severe impairment in aspects such as their own quality of life, daily functioning, and physical aggression compared to cases without depression. This suggests a worse prognosis when depression is present alongside Alzheimer's disease.[13]

(7) S-IADL (Seoul-Instrumental Activities of Daily Living score)

Instrumental Activities of Daily Living (IADL) is a tool used to assess more complex functions necessary for older adults to maintain independent living. It evaluates abilities such as using the telephone, going out or traveling, shopping, meal preparation, household chores, manual tasks (sewing or nailing), laundry, proper medication management, and financial management.

(8) Electroencephalogram (EEG)

It records the brain's electrical activity in terms of frequency and amplitude, represented as an electroencephalogram (EEG). By analyzing the location of the electrical activity and the waveform of the brainwaves, it can diagnose abnormal electrical states within the brain and assess the degree

of arousal and brain activity in healthy individuals. In this study, resting-state EEG will be measured for 7 minutes each under conditions of eye closed and eye open.

(9) ECG

It is a test to determine the presence of heart disease, with a duration of approximately 10 minutes per test session.

(10) DTI (diffusion tensor image) (visit 3, visit 26)

The fractional anisotropy (FA) value, which reflects the movement of water molecules in white matter, is a measure of the integrity of white matter. By measuring the FA values of white matter connecting memory networks, it can be observed that these values are lower in early dementia or mild cognitive impairment compared to normal conditions. The hypothesis is that through transcranial magnetic stimulation (TMS), these values will increase, and this will be investigated in the study.

(11) resting functional MRI (visit 3, visit 26)

After administering TMS stimulation, changes in the functional connectivity of the memory network between the hippocampus and the cortex will be qualitatively compared using oxygen-dependent images (blood-oxygen-level-dependent images, BOLD) through resting-state fMRI analysis. In early dementia or mild cognitive impairment, functional connectivity is often reduced. The hypothesis is that through transcranial magnetic stimulation, the connectivity of the memory network will be enhanced, and this will be investigated in the study.

(12) Randomization and Participant Enrollment Number Assignment

Participants who consent to participate in the clinical trial and meet the inclusion/exclusion criteria will be enrolled, and randomization will be conducted. They will be randomly assigned to two groups and assigned a code. The clinical trial medical device will then be applied to the participants in the order of their enrollment.

- rTMS group: rTMS for 4 weeks

- sham group: Sham stimulation (using a sham coil producing only sound without actual rTMS stimulation) will be administered for a duration of 4 weeks.

Randomly assigned participants will be assigned participant registration numbers as follows:

Registration Number: SMC-Year Code-Trial Serial Number-Sequential Number

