#### 2) Secondary objective

- Comparison Before and After Stimulation in the rTMS Group:

-The change in CANTAB PRM, RVP, and SWM scores at 4 and 8 weeks after 4 weeks of repetitive Transcranial Magnetic Stimulation (rTMS) applied to the parietal region was measured to assess cognitive function changes.

-The change in K-MMSE, K-MoCA, CDR-SOB, COWAT, Stroop, and TMT scores at 4 and 8 weeks after 4 weeks of rTMS treatment was measured and compared with baseline scores to assess cognitive function changes.

-The change in ADAS-Cog scores at 4 weeks after 4 weeks of rTMS treatment was measured and compared with baseline scores to assess cognitive function changes.

-The change in K-GDS short form scores at 4 and 8 weeks after using rTMS was measured and compared with baseline scores to assess emotional changes.

-The change in S-IADL scores at 4 and 8 weeks after using rTMS was measured and compared with baseline scores to assess changes in daily life functions.

-The change in FA (fractional anisotropy) values through diffusion tensor image (DTI) analysis **at 4**

weeks after using rTMS was measured and compared with baseline to assess white matter microstructure changes.

-The qualitative assessment of functional network changes in resting-state fMRI at 4 weeks after using rTMS was conducted by comparing with baseline, involving correlation, coherence, and spatial grouping based on temporal similarities in BOLD images to analyze simultaneously activated brain regions.

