#### ●Comparison Between the Experimental Group and the Control Group (Sham Group):

- A comparison of changes in K-MMSE, K-MoCA, CDR, ADAS-Cog, COWAT, Stroop, TMT/PRM, RVP, and SWM scores between the rTMS stimulation group and the sham group.
- A comparison of changes in MRI DTI analysis, specifically FA values, between the rTMS stimulation group and the sham group.
- A qualitative comparison of functional network changes in fMRI between the rTMS stimulation group and the sham group, focusing on assessing alterations in connectivity patterns.

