#### 2) Secondary Outcome Measure

- 1) Study Design: Single-arm design
- 2) Allocation: Random assignment
- 3) -Compare changes in K-GDS short form and S-IADL scores between baseline, 4 weeks after rTMS stimulation, and 8 weeks after.  
-Compare changes in K-MMSE, K-MoCA, CDR-SOB, ADAS-Cog, COWAT, Stroop, TMT, RVP, SWM, PRM scores between baseline and after 4 weeks of rTMS stimulation.  
-Compare FA values in DTI analysis at 4 weeks after rTMS stimulation.  
-Examine functional network changes in resting-state fMRI at 4 weeks after rTMS stimulation.
- 4) masking: Blinded assessment by evaluators

- 1) Study Design: Parallel design
- 2) Allocation: Random assignment
- 3) Intervention Group: rTMS application group  
Control Group: Sham group (sham coil emits sound only, no rTMS stimulation)
- 4) -Compare K-MMSE, K-MoCA, CDR, ADAS-Cog, COWAT, Stroop, TMT, RVP, SWM, PRM scores between intervention and control groups after 4 weeks.  
-Compare FA values in DTI analysis between intervention and control groups at 4 weeks after.  
-Examine functional network changes in resting-state fMRI between intervention and control groups at 4 weeks after.
- 5) masking: Blinded assessment by evaluators

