#### **D. Masking**

In this clinical trial, "blinding of evaluators" will be maintained.

① Participants: The stimulation coil with 8-shaped design is capable of mode changes. In the sham mode, a sound similar to the sound of the magnetic field being generated will occur, but no actual magnetic field will be generated. In the active mode, a real magnetic field will be generated, providing rTMS stimulation. The appearance of the device, sound, and the time of applying the rTMS coil are the same. Participants who are receiving rTMS stimulation for the first time may find it difficult to discern whether they are receiving active or sham stimulation. However, participants who have experienced the trial device at least once before may feel sensations or discomfort when receiving active stimulation, making complete blinding challenging.

② Operator: The individual delivering the rTMS stimulation will select either the sham or active mode from the coil, making them unblinded.

③ Investigator (Principal Investigator): The investigator enrolls patients who meet the criteria and are willing to participate in the study, as well as verifies patient conditions during outpatient visits. However, they will remain blind to which group the patients are assigned to.

④ Evaluator: Three independent assessors will evaluate cognitive function. These assessors will be blinded to which group the patients are assigned to.

⑤ Emergency Unblinding Procedure: In case of severe medical emergencies on a case-by-case basis, unblinding by the investigator might be considered. If the trial responsible person deems unblinding necessary, it will be performed. In such cases, the trial responsible person will ensure records of the unblinding procedure are maintained.

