#### **E. Stimulation Protocol**

-Stimulation Frequency: 20 Hz, delivering stimulation at 20 Hz for 2 seconds in each train, followed by a 28-second rest period. A single stimulation site will receive a total of 40 trains (a total of 1600 pulses) in one session.

Stimulation Intensity: 100% of the motor threshold (MT), which can be decreased to 70% of the motor threshold in case of pain. Motor threshold is determined by stimulating the contralateral

motor cortex with TMS for 10 trials while the target muscle (Abductor pollicis brevis) is at rest. The lowest intensity that elicits visible muscle contractions in the target muscle for 5 out of 10 trials is selected as the motor threshold. This measurement will remain constant throughout the 4-week stimulation period.

-Stimulation Site: The stimulation site will be determined based on the resting functional MRI analysis of the baseline scan. The left lateral parietal region with the highest connectivity to the hippocampus will be selected for stimulation. During the 4-week stimulation period, an individualized medical guide will be used to fix the TMS transducer on the patient's scalp for accurate and consistent targeting. This medical guide will be produced using 3D printing based on the patient's brain MRI information, ensuring a customized fit for each patient.

-Duration: More than 20 minutes per session. Stimulation Period: Stimulation will be administered 5 times per week (Monday to Friday) for a total of 20 sessions over a 4-week period.

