|     |                  |                                                                                                          |
|-----|------------------|----------------------------------------------------------------------------------------------------------|
|     | K-GDS short form | Change in K-GDS short form score at 4 weeks and 8 weeks after the intervention.                          |
| MRI | DTI              | The change in fractional anisotropy (FA) values after 4 weeks                                            |
|     | Resting fMRI     | A qualitative analysis using BOLD (blood-oxygen-level-dependent) images will be conducted after 4 weeks. |

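### Resting fMRI carries a directional connectivity hypothesis, but the protocol fixes a qualitative comparison with no chosen measure and does not secure masking of whoever reads the images

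*Protocol*

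**What the plan says.** **Hypothesis.** Protocol section 10.A(11) expects that through stimulation "the connectivity of the memory network will be enhanced, and this will be investigated in the study". The network meant there is the one linking hippocampus and cortex.

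**Method.** The same section says that changes "will be qualitatively compared using oxygen-dependent images (blood-oxygen-level-dependent images, BOLD) through resting-state fMRI analysis". The outcome table in section 13.1.B has "A qualitative analysis using BOLD (blood-oxygen-level-dependent) images will be conducted after 4 weeks". The between-group objectives in section 6.A have "A qualitative comparison of functional network changes in fMRI between the rTMS stimulation group and the sham group", and the synopsis describes the between-group item in the same way. The within-group objective in section 6.A also calls the assessment qualitative, but describes it as "involving correlation, coherence, and spatial grouping based on temporal similarities in BOLD images to analyze simultaneously activated brain regions".

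**Masking.** Section 9.A, under the secondary outcome measures, has two blocks that list resting fMRI. One is single-arm. The other is parallel: "Examine functional network changes in resting-state fMRI between intervention and control groups at 4 weeks after". Each block ends with a line giving blinded assessment by evaluators. Section 9.D then says who the evaluators are: "Three independent assessors will evaluate cognitive function", blinded to group. The synopsis calls the three of them neuropsychologists.

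**Site.** Section 9.E bases the stimulation site on the baseline resting fMRI scan: "The left lateral parietal region with the highest connectivity to the hippocampus will be selected for stimulation". A positioning guide is made for each patient, with no arm excepted.

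**The concern.** A hypothesis with a direction needs a quantity that can go up or down, and a rule for comparing it. The protocol supplies the hypothesis but labels the comparison qualitative. This is a stated choice of method, not detail held over for an analysis plan. It also sits badly with section 13.2, which says the trial is meant to explore how large the differences in the primary and secondary variables are. DTI, the other imaging outcome, has a numerical endpoint (fractional anisotropy); resting fMRI has none.

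Two things are at stake. A qualitative reading gives nothing that a later confirmatory trial can use for planning, although section 7.D says that helping to size such a trial is a purpose of this one. A reading that leaves room for judgement, with a known expected direction, is also open to expectation bias unless the reader is masked to arm and to which scan came first.

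A third matter bears on how a numerical result should be read. The scan that picks the stimulation site is also the baseline scan of the outcome, so before/after change at that site is exposed to regression to the mean.

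**Working it through.** The protocol gives no effect size, SD, alpha or power for this outcome, so there is no figure to reproduce.

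**1. Is a measure fixed?**

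- Section 10.A(11): network connectivity, directional hypothesis, qualitative comparison; no region or scale.
- Section 6.A, within group: qualitative, involving correlation, coherence and spatial grouping; none is selected as the outcome.
- Section 6.A, between groups, and the synopsis: qualitative comparison.
- Section 13.1.B: qualitative analysis.
- Section 9.A: examine changes; no measure.
- Section 13.2: a linear mixed-effects model with group and time. It needs one number per participant and time point, and none of the sections above defines that number for fMRI.

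Numbers will nevertheless exist. Choosing the site with the strongest hippocampal connectivity (section 9.E) means ranking candidate sites by a connectivity value in every participant.

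**2. Is the reader masked?** Section 9.A attaches blinded evaluators to the fMRI blocks. Section 9.D goes role by role (participant, operator, investigator, evaluator), and its evaluators assess cognition. No imaging reader or analyst appears. The sections do not settle whether the masking line reaches the images, and nothing addresses scan order.

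**3. What does choosing the site as the baseline maximum do?** Assumptions, none from the documents: k independent candidate sites of equal mean, total SD 1, test-retest reliability ρ, no treatment effect.

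Expected change at the selected site = −(1 − ρ) × E[max of k standard normals], with E[max] = 1.54 for k = 10 and 2.25 for k = 50.

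- Mildest case, k = 10, ρ = 0.7: −(0.3 × 1.54) = −0.46 SD.
- Strongest case, k = 50, ρ = 0.4: −(0.6 × 2.25) = −1.35 SD.

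A simulation of 4,000 trials per setting, 16 per arm, with ρ from 0.3 to 0.9, gave the following:

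| Quantity | k = 10 | k = 50 |
|---|---|---|
| Mean change within rTMS arm, no effect | −0.16 to −1.08 | −0.22 to −1.58 |
| Significant false decrease within arm | 26% to 97% | 48% to 100% |
| Significant false increase within arm | at most 0.1% | 0.0% |
| Between-arm difference, no effect | at most 0.004 in size | at most 0.003 in size |
| Between-arm type I error (nominal 5%) | 4.6% to 6.0% | 4.6% to 4.9% |
| Between-arm estimate, true effect 0.5 SD | 0.49 to 0.50 | 0.50 |

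With k = 10, ρ = 0.5 and a true gain of 0.5 SD, the mean change within the rTMS arm was −0.28 SD: a real gain at the target would look like a loss. The between-arm estimate in the same setting was 0.49.

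**4. How precise would a numerical comparison be?** With 16 per arm, complete data and no adjustment, the 95% half-width is t(0.975; 30) × √(2/16) = 2.042 × 0.354 = 0.72 SD. If baseline and follow-up correlate at 0.4 to 0.7 (an assumption), adjustment multiplies this by √(1 − r²), which is 0.92 to 0.71, giving about 0.66 to 0.52 SD. These are SDs between participants. The SDs in step 3 are across candidate sites, so the two sets should not be compared.

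**The case against.** The strongest reply is that this is one secondary imaging item in a trial that calls itself exploratory and descriptive, and that section 6.A already names computed quantities. Region, transformation and model can properly be left to an analysis plan, which may exist. Much of this stands. The form of the summary is a matter of choice, and the documents do not exclude numerical work. What remains is that the protocol does not stay silent: it calls the comparison qualitative in four sections, and an analysis plan that specified a numerical comparison would have to depart from all of them.

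Three stronger readings are tempting, and the documents do not support them.

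- A reader might infer that the connectivity hypothesis cannot be tested without bias. The site is chosen in the same way in both randomised arms, so the selection effect cancels in the rTMS-versus-sham comparison, which is already planned. The hypothesis also concerns the wider hippocampus-cortex network. No section makes connectivity at the stimulated target an outcome.
- A reader might infer that the images are read unmasked. Section 9.A attaches blinded assessment to the fMRI blocks, and section 9.D declares only the operator unblinded. No section says that the imaging reader knows the arm.
- A reader might infer that site selection can push a within-arm result either way. It acts only downward, against the hypothesis. An upward error would have to come from the reading itself, which the documents do not show.

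**Conclusion.** The point holds as a flaw of method and a gap in masking. The protocol pairs a directional hypothesis with a qualitative comparison and no chosen measure, so as written this secondary outcome yields no effect size or interval. Sections 9.A and 9.D do not agree clearly on whether masking covers the imaging reader.

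The randomised comparison is not invalid. The regression effect matters only if connectivity at the stimulated target is reported as a before/after change within an arm. Its direction is then known (downward), but its size is not: 0.46 to 1.35 SD rests on assumed numbers of sites and assumed reliability, and moves with both. The calculation also treats sites as independent and equal in mean, which neighbouring cortical areas will not be.

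The change is worth making because it is cheap and improves what the trial can report. It does not touch the primary outcome.

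**What to change.** 1. In the synopsis and sections 6.A, 10.A(11) and 13.1.B, replace the qualitative comparison with one numerical measure named in advance. An example is mean Fisher-z connectivity between the hippocampus and a memory network whose regions are defined independently of the individual target. Qualitative maps can stay as illustration.
2. Estimate the rTMS-versus-sham difference at follow-up, adjusted for the baseline value, with a 95% interval, and label it exploratory.
3. In section 9.D, add the imaging analyst as a role masked to arm and scan order, by coding the files before analysis.
4. If connectivity at the stimulated target is also reported, interpret it only between arms and say why.

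Before the time point of the measure is fixed, one related discrepancy must be reconciled: section 10.A(11) places the follow-up scan at visit 26, which the schedule labels week 8, while sections 6.A, 9.A and 13.1.B say 4 weeks.

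The cost is a modest amount of analysis on scans already planned, plus file coding. The downside is a wide interval: a half-width of about 0.72 SD unadjusted with 16 per arm. A published interval makes that imprecision visible; a qualitative reading hides it.
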